#### ***Recruitment***

Recruitment for the study began in April 2012. The recruitment goal is to enroll 36 practices total, randomized into the two study arms. To date, 29 practices have been enrolled in the study. 25 of these practices have been randomized in two waves. The intervention period for the first wave of 18 practices began in January of 2013. The intervention for the second wave of seven practices will begin in June of 2013. We plan to recruit and randomize all additional practices by the end of 2013. Consent was obtained at multiple levels; a practice administrator signed a practice agreement and data use agreement for each individual practice organization. From each individual practice site (cluster), informed consent was obtained from a site coordinator and a lead physician at each site, as representatives of the cluster. Consent was obtained prior to randomization.

#### ***Randomization protocol***

In cases where two or more selected practices were drawn from the same multi-practice organization, contamination was limited by checking for clinician overlap. If overlap was minimal, organization was used as a stratification variable; if overlap was potentially problematic in terms of contamination, practices were constrained to be in the same group. From the pool of available practices, pre-study information from electronic health record (EHR) data on baseline performance characteristics related to CKD or in general and variables which may influence outcome measures, including practice and patient panel characteristics as well as pre-study clinical measures were collected (full-time equivalent physicians, mean HbA1c, % diabetic, % stage four CKD, % of diabetics with HbA1c >9, mean GFR, mean SBP, % with SBP >130, % with SBP >140, % African American, % Hispanic, % uninsured) [34]. Stratification variables included geographic region and organization. All possible combinations of the 18 eligible practices into two groups of nine were generated [35] using the IML procedure in SAS [36], retaining order so that the first designated group would be assigned to the intervention, the remaining practices to controls (n = 48,620). Only randomizations that were balanced on stratification variables were retained (n = 1,728). For each randomization, a balance criterion (defined as the sum of squared differences on standardized variables between control and intervention groups) was computed. After examining the distribution of the balance criterion, a maximum allowable difference between the groups was established and an optimal set of randomizations identified (n = 136). From this set, one was chosen using a random number generator and practices were assigned to treatment or control arms. This process was repeated for the next group of seven practices, including a dummy practice in the randomization procedure to accommodate the uneven number of practices. The remaining practices will be randomized using the same protocol. As with all CRCTs, patients are not randomized *per se*; they are assigned to treatment conditions along with the medical practices in which they receive care.

#### ***Power analysis***

Given the CKD national prevalence rate of 13% and an expected average of 5,500 active patients per practice, we expect roughly 715 CKD patients per practice (this estimate is supported by a recent analysis of >110,000 individuals with stage three or four CKD drawn from over 100 DARTNet practices.) With 18 practices per arm and a minimum of 200 patients per practice (smallest practice estimated at 2,000 patients with a conservative 10% prevalence of CKD over life of study) there will be a minimum of 3,600 patients per arm (actual expected sample size is over 14,000 per arm.) A sample size of 3,600 per arm will provide >80% power to detect a 0.18 effect size difference between two arms at a single time point if the intra-class correlation (ICC) is 3%. This effect size was assumed based on previous results from the diabetes TRANSLATE study [32]. In terms of change over time, a sample size of 3,600 will provide >80% power to detect a small linear trend effect, increasing from 0 at baseline to 0.2 standard deviation (SD) at final follow up, with four observations per person and an ICC of 3%, with a random effects structure with random intercept and random slope [37].

#### ***Intervention design***

Four elements of the TRANSLATE method will be implemented in both groups, while the remaining ones will apply to facilitated practices only. All interventions will occur at the cluster level, and there will be no randomization or specific intervention undertaken for individual patients. The CDS-only practices will have CKD decision support algorithms based on the Kidney Disease Outcomes Quality Initiative (KDOQI guidelines added to their existing CDS. There will be three separate vendors that will be providing point of care support for the study. Computer Integrated Networks of America (CINA), Health Metrics Systems (HMS), and an EMR with integrated CDS Medent. All practices will receive one session of introductory academic detailing [38] concerning the rationale for the algorithms. They will also be provided related technical support on request. Facilitated practices will receive the CKD-specific CDS, as well as a practice facilitator to assist them in the implementation of the full TRANSLATE model (Table 1).

**Table 1 T1:** Translate elements by intervention arm

**TRANSLATE elements that will be used in both arms**	
**T**arget:	Common targets will be set for all practices and tracked through the CKD tool. The CDS-only practices will receive a quick reference guide for the treatment of CKD
**R**egistry and reminder systems	CINA created a CKD registry and will maintain it throughout the study period. Point-of-care decision support specific to CKD will be provided to practice staff and physicians prior to patient visits.
**A**dministrative buy-in	Obtain consent from each practice and all practice sites asked to identify a physician champion and site coordinator to oversee study implementation at their site.
**N**etwork Information systems	The information systems (EHRs and CDS) will be used to create system level reports across all practices.
**TRANSLATE element that will be used only in facilitated CDS practices**	
**S**ite coordination	A site coordinator at each practice will assemble a quality improvement (QI) team that will meet monthly to review performance data regarding CKD. The site coordinator will also work with the clinicians and practice staff to implement workflow changes such as pre-visit planning, standing orders, and patient education materials to improve efficiency of disease management. In addition, the site coordinator will be in contact with the practice facilitator by videoconference for assistance and advice.
**L**ocal physician champion	This person will be the clinician leader and educator for other providers in each practice. Responsibilities will include supporting the site coordinator and the QI team. This physician will be in contact with the academic mentor for the practice regarding clinical questions about CKD and will participate in learning collaboratives with the site coordinator.
**A**udit and feedback	Practice, individual provider, and patient-level outcome reports for the intervention practices will be generated through CINA regarding the seven performance measures (BP, HbAIC, LDL, use of ACE/ARB, referral to a nephrologist, smoking cessation and avoidance of NSAID or Cox-2) and will be reviewed by the team. Reports will also be reviewed quarterly with the practice facilitator by videoconference. The videoconference will allow the facilitator to learn what worked in each practice and to share what other practices have implemented successfully.
**T**eam approach	A quality improvement (QI) team consisting of the local physician champion, site coordinator and nursing, front office, and administrative staff will meet monthly to review progress of the CKD project. Workflow changes will be recommended and tested.
**E**ducation	An educational program using academic detailing and practice facilitation and videoconferencing will be utilized to support the practices’ efforts. All facilitated practices will be assigned an academic practice mentor. This mentor will be available to the office physician champion and practice coordinator to answer any questions and discuss plans. The academic mentor will review the practice’s data and participate in a quarterly videoconference with either the study coordinator or the lead clinician to review progress on the project.

#### ***Facilitation protocol***

The facilitators' overall role is to help the practices implement the TRANSLATE model to improve guideline-concordant care for CDK. The facilitator will assist with the site coordination, physician champion's needs, audit and feedback, team approach, and education. Two practice facilitators are each assigned to half of the CDS+ facilitation practices. Throughout the course of the intervention period, the facilitators will engage in virtual interactions with the practices, in which they will work with practice quality improvement (QI) teams to identify and solve issues specifically related to their care of patients with CKD and form and maintain relationships with each practice. Facilitation objectives include: assisting practices in setting goals to implement CKD guidelines; helping practice teams, strategize, test, and implement change; facilitating meetings and fostering a continuous QI culture; serving as a liaison for data and performance feedback; and sharing best practices and linking intervention practices.

Due to the national scope of this project, facilitation contacts will occur ‘virtually’ using videoconferencing (GoToMeeting®), phone, and e-mail. General communication will entail a minimum of once monthly teleconferences with each practice’s site coordinator to review the status of the project, monthly virtual QI team meetings, monthly calls between the academic mentors and the lead physician, periodic learning collaboratives, and a benchmarking webinar every six months with the academic detailing team.

### Data collection

#### ***Clinical data***

From practice EHRs, we will collect the measurements outlined in Table 2. Medication fulfillment data will be collected from Surescripts RxHub through CINA or the practice EHR. Death will be determined from information in practice EHRs or from linkages to the National Death Registry. We will check for deaths among patients who have not made any visits in the prior 12 months in the first two years of the intervention and in the prior six months in the final year of the intervention. Medicare claims data will be obtained before and after the intervention to allow for a proper cost analysis.

**Table 2 T2:** Clinical data elements

**Data element**	**Measure type**
Year of birth	Numerical
Gender	M/F
Race/ethnicity	Standard major groups and Other
Current smoking	Current, never, past
Height and weight/BMI	Hgt, wgt actual
Total visits/encounters	Encounter records
Hemoglobin	Numerical result
HDL	Numerical result
LDL-C	Numerical result
Triglycerides	Numerical result
Creatinine	Numerical result
AST	Numerical result
ALT	Numerical result
HbA1c	Numerical result
25 OH Vitamin D	Numerical result
Electrolytes	Numerical result
Serum phosphorous	Numerical result
PTH intact	Numerical result
All medications	Coded (NDC)/RxNorm
All diagnosis – active & inactive	ICD-9
Blood pressure	Systolic and diastolic
Estimated GFR	Calculated value
Urine albumin/creatinine ratio	Calculated value
Medicare insurance coverage	Flag for medicare insurance
Nephrologists referrals	Referral records (when available)

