## Background

Chronic kidney disease (CKD) and end stage renal disease (ESRD) are steadily increasing in prevalence in the United States (US) [1]. In 2000, there were 26 million American adults with CKD, and this represented a 30% increase over the past decade [1]. The annual incidence of ESRD is projected to increase from its 2007 level of 111,000 to 143,000 by 2020, when the total US population of people with ESRD is expected be over 770,000 [2,3]. The aging of the population and the rising prevalence of obesity, hypertension, and type 2 diabetes—the major risk factors for CKD—contribute to this trend [4]. CKD is a serious condition; stage three CKD is associated with a five-year all-cause mortality rate of 24.3% and a five-year need for renal replacement of 1.3%. Stage four CKD is associated with a five-year 45.7% mortality rate and a five-year 19.9% requirement for renal replacement [5].

While there is reasonable evidence that specific activities can be implemented by primary care physicians (PCPs) to delay CKD progression and reduce mortality [6-12], CKD is under-recognized and undertreated in primary care offices [13-15] and PCPs are generally not familiar with treatment guidelines [13,14]. Even when diagnosed, CKD is a chronic condition that, like diabetes, is frequently associated with co-morbidities, making effective treatment difficult due to the complexity of care.

The reasons for the slow rate of progress in improving healthcare delivery, especially for chronic conditions such as CKD, are complex. Rogers [16], in his classic studies of diffusion of innovation, outlined several potential barriers to adoption of innovation in many industries. These included lack of time and monetary resources, as well as organizational inefficiencies [16]. The health sector has been notoriously slow to adopt new approaches to care [17]. Competing demands and time limitations often inhibit the ability of PCPs to adopt evidence-based preventive services and manage chronic diseases well [18,19], and it takes several years for known evidence to become common practice [20-22].

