#### ***Hypothesis 2.2***

Patients with stage three and four CKD in facilitated practices will have significantly lower all-cause mortality than stage three and four patients in CDS-only practices.

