#### ***Data analysis for hypothesis 2.2 (all-cause mortality)***

All-cause mortality will be confirmed using the National Death Index to determine the exact date of death. The outcome for the analysis will be time from baseline to death. Patients who are alive at the end of the study period will be censored at the end of the follow-up time. Assumptions of the proportional hazards model will be checked for each variable. Covariates will include baseline eGFR, defined as the mean of the last two eGFRs prior to study entry, as well as socio-demographic and clinical characteristics.

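### The active death check is triggered by absence of visits, but censoring runs to study end, so some late deaths in recently seen patients can be counted as survival

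*Protocol article*

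**What the plan says.** The Clinical data paragraph under Data collection names two sources: "Death will be determined from information in practice EHRs or from linkages to the National Death Registry". The first covers every patient. For the active check the article then says who is looked up: "We will check for deaths among patients who have not made any visits in the prior 12 months". That window governs years one and two; later the check covers those without a visit "in the prior six months in the final year of the intervention".

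The analysis section for Hypothesis 2.2 adds: "All-cause mortality will be confirmed using the National Death Index to determine the exact date of death". Its censoring rule is: "Patients who are alive at the end of the study period will be censored at the end of the follow-up time". The hypothesis is that patients in facilitated practices "will have significantly lower all-cause mortality than stage three and four patients in CDS-only practices".

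The Cost-effectiveness analysis section (under Data analysis) names National Death Index mortality among the data used to calculate QALYs. Nowhere does the article state a search of all patients at study end, or tie the censoring date to the date at which vital status is complete.

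**The concern.** The two rules do not fit together. Censoring at the end of follow-up treats each patient without a known death as observed alive to that date. The active check does not establish this for patients with a visit in the last six months. Someone seen four months before the end who dies two months before it does not meet the condition for being looked up. Unless the practice EHR holds the death, that patient contributes survival time to the end.

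Whether a patient is looked up depends on visits made after randomisation, and whether an unsearched death is found depends on EHR recording. Both could differ by arm: the Site coordination row of Table 1 gives facilitated practices alone pre-visit planning and other workflow changes. If they do differ, the comparison for Hypothesis 2.2 is biased, and the QALYs built on the same mortality data with it.

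**Working it through.** **Plan's own figure.** The article gives no event count or power for mortality, so there is no mortality figure to reproduce. Its power statement concerns a 0.18 effect size with 3,600 per arm and ICC 3%. The design effect is 1 + 199 × 0.03 = 6.97, and the effective size is 3,600 / 6.97 = 516 per arm. Power is 82.5% (two-sided 5% level assumed), in line with the stated figure of over 80%. That statement is not at issue here.

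**Inputs from the article**
- Background: "stage three CKD is associated with a five-year all-cause mortality rate of 24.3" per cent.
- Power analysis: 18 practices × 200 patients = 3,600 per arm.
- Follow-up: up to 36 months (Hypothesis 1.1 analysis), and at least 18 months of intervention (Trial status).
- Six-month visit window at the end, applied here to both durations.

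**Assumptions, not in the article.** Constant hazard; Poisson visits at rate v per year; the last check run on the censoring date; EHR capture e of otherwise unsearched deaths.

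**Step 1: deaths in the last six months.** h = −ln(1 − 0.243)/5 = 0.0557 per year. Deaths by time T are 3,600 × (1 − exp(−hT)). Those in the last half year are 3,600 × (exp(−h(T − 0.5)) − exp(−hT)).
- T = 3 years: 86 of 554 per arm, 15.5%.
- T = 1.5 years: 93 of 288 per arm, 32.4%.

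The final check catches earlier deaths, because those patients then have no visit in the window.

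**Step 2: share of late deaths not searched.** The patient must have had a visit inside the window before dying. Averaged over the window this share is m(v) = 1 − (1 − exp(−0.5v))/(0.5v).

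| Visits per year | m(v) | Missed, 36 months (e = 0) | Missed, 18 months (e = 0) |
|---|---|---|---|
| 1 | 21% | 18 (3.3% of all deaths) | 20 (6.9%) |
| 2 | 37% | 32 (5.7%) | 34 (11.9%) |
| 4 | 57% | 49 (8.8%) | 53 (18.4%) |
| 6 | 68% | 59 (10.6%) | 64 (22.1%) |

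Each missed count is multiplied by (1 − e): it halves at 50% EHR capture and falls to one fifth at 80%. With the article's stage four mortality (45.7% at five years, h = 0.1221) the missed percentages are similar: 3.0% to 9.7% at 36 months and 6.7% to 21.4% at 18 months.

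**Step 3: what an arm difference would do.** The true hazard ratio is set to 1, and s is the late share from Step 1. The observed fraction of deaths in an arm is 1 − s × m(v) × (1 − e). The ratio is facilitated over CDS-only.

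| Scenario | 36 months | 18 months |
|---|---|---|
| 4 v 3 visits a year, e = 0 | 0.986 | 0.967 |
| 4 v 2 visits a year, e = 0 | 0.967 | 0.926 |
| 4 v 2 visits a year, e = 50% | 0.984 | 0.966 |
| 4 visits in both arms, e = 80% v 50% | 1.028 | 1.061 |
| Same visits and same e in both arms | 1.000 | 1.000 |

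For scale, ignoring clustering, the standard error of the log hazard ratio at 3,600 per arm is about √(2/554) = 0.060 at 36 months and √(2/288) = 0.083 at 18 months. The largest shift, ln 0.926 = −0.077, is 0.077/0.083 = 0.9 standard errors. At the 14,000 per arm that the article expects, the standard error shrinks by √(3,600/14,000) = 0.51, so the same shift is 1.8 standard errors before clustering widens it.

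**The case against.** The strongest defence is that the article does not say when the last check is run. If it is run six months or more after the censoring date, every patient dead by that date has no recent visit and is searched, so nothing is lost. The check can also be read as surveillance during the intervention, with the National Death Index serving the analysis as a whole. Linkage timing is the sort of detail that an article leaves to the full protocol.

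This shows that the defect can be cured by clarification, not that the text is sound. The article does state who is checked. The Hypothesis 2.2 section has the index confirm deaths and supply dates, which does not widen the search. The cost-effectiveness section only names it as a source. If a full search was meant, the Clinical data paragraph contradicts it.

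A second defence is that EHR deaths count for every patient. That is correct and limits the loss. Its extent is unknown: Table 2 lists no date of death or vital status, and a check triggered by absent visits suggests that the EHR alone was not thought sufficient.

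Two stronger readings are tempting. A reader might infer that the deaths of the last six months are missed altogether. They are not: patients without a visit in that window are searched, and EHR-recorded deaths are found. A reader might also infer that facilitation raises visits and so biases the result toward benefit. The article does not say that facilitation raises visit frequency; Table 1 describes workflow and staff meetings. Better EHR recording of deaths in facilitated practices would push the other way.

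**Conclusion.** The point holds in limited form. Followed as written, the plan can carry some late deaths in recently seen patients as survival to study end. Under the assumptions above, with no EHR capture, the loss is about 3% to 11% of all deaths at 36 months and 7% to 22% at 18 months. It shrinks in proportion to EHR capture, and is nil if the final check falls at least six months after the censoring date.

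Equal losses in both arms leave the ratio of observed deaths unbiased. Unequal losses bias it in a direction that the article does not allow one to predict; the scenarios above range from 0.93 to 1.06. Visit rates and EHR capture by arm are assumed, so these figures mark a range and are not estimates. The bias is probably modest. The guideline-concordance score of Hypothesis 1.1 is not affected. This should be fixed, because ascertainment of a named outcome rests on events after randomisation and the remedy is simple.

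**What to change.** Preferred: replace the visit-triggered rule for the analysis with one full search. Possible wording:

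> Every patient in the mortality analysis set, in both arms, will be submitted to the National Death Index through one common closing date, regardless of visit history or EHR information. Patients with no death found by that date will be censored on that date.

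The cost is some extra submissions. Visit-triggered checks can continue as surveillance during the intervention.

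Alternative: keep the visit trigger but set the mortality censoring date at least six months before the final check, with the six-month rule applied to all patients at that check. Each patient then either has a visit after the censoring date, and so was alive on it, or was searched. This is not free: it needs a later final check or gives up to six months of follow-up. On the figures above, giving up the full six months would discard about 16% (36 months) to 32% (18 months) of deaths, more than the visit trigger is likely to miss.

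In either case, state the date of the final search and use one name for the source, which is called a Registry under Data collection and an Index under Data analysis.
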